### General demographics and medical history

The CORE-VNS registry is designed to be the largest, prospective, international data set ever collected of people receiving VNS for DRE. This creates an opportunity to assess the global demographic profile of people who receive adjunctive VNS. Regional variances in age, sex, ethnicity, race, aetiology (structural, genetic, infectious, metabolic, immune, unknown), epilepsy syndrome (childhood absence, juvenile absence, juvenile myoclonic, infantile spasms, West, Dravet, Lennox-Gastaut, tuberous sclerosis, continuous spikes/slow waves during sleep, electrical status epilepticus, epilepsia partialis continua, unknown, other), epilepsy type (focal, generalised, combined, unknown), history of brain surgery, family history of seizures, comorbidities, duration since epilepsy diagnosis and medical history of people who proceed to VNS will be investigated. Furthermore, we aim to better understand the prescribing history of failed ASMs in the DRE population.

### Use of VNS in genetic epilepsies

At some institutions participating in the CORE-VNS registry, genetic profiling of patients with DRE is included as part of their medical assessment. In clinical application, VNS has often been applied in cases of putative genetic epilepsies, for example, Dravet syndrome, some cases of Lennox-Gastaut syndrome and other epileptic encephalopathies, even if the therapy has not been directly investigated within these populations in randomised clinical trials. We will capture the regional practices of genetic testing in DRE as well as exploring the frequency of use of VNS in those with confirmed/suspected genetic epilepsy. We will examine the effectiveness of VNS on seizure and non-seizure outcomes in these patients. Due to the wide range of genetic mutations contributing to epilepsy and as the registry is open to all-comers, it is impractical to a priori define subpopulations for this analysis.

### Regional practice and feature use

This registry aims to better understand regional differences in the implementation of VNS. Specifically, there is interest in identifying regional variances in clinical and safety outcomes associated with different implementations of VNS dosing and standard clinical practice. Newer models of VNS devices have only recently become available in some of the regions participating in the registry, so differences may be apparent in the use of new features. The features available in these newer models offer more programming flexibility and the potential for improved clinical and safety outcomes, but may also add complexity to the therapy. In this study, rationale for the selection of a Model 1000 ‘SenTiva’ generator is collected by ranking the relative importance of each feature in the eventual decision. The rationale options for device or feature selection include: scheduled programming, day/night programming, low heart rate detection, prone position detection, events and trends, availability of AutoStim with a smaller generator.

### Titration guidance and scheduled programming

The primary limitations of previous studies of VNS in providing quality guidance on dosing and titration were limited sampling of all device parameter combinations and lack of programming data collected during the titration period.^27–30^ CORE-VNS will collect detailed titration data prospectively. A generalised linear mixed model will be developed to assess the sensitivity of clinical and safety outcomes to specific programming settings. The relationship between time-to-dose and time-to-response will be assessed using a Cox proportional hazard model to characterise the impact of rapid titration (titration in <3 months) on clinical outcomes, as opposed to slow titration (>6 months). Titration period will be defined as time taken to achieve either an optimal programming output as defined by the mixed model, or as time taken to the reach the minimum recommended output current defined in the device manual.

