### Clinical endpoints

Beyond information on demographics, medical history and genetics (where applicable) in the global DRE population, the registry aims to gather a broad range of clinical outcome measures to assess the purported benefits of VNS. The clinical endpoints of the registry include data collection at baseline as well as 3, 6, 12, 24 and 36 months after implant. Long-term follow-up data may continue annually through 60 months after implant where applicable (table 2).

**Table 2 T2:** Protocol-specified visit schedule and assessments for participants in the CORE-VNS registry. After the first year, patients will return to the clinical site for annual visits, where all endpoint measures will be assessed. At unscheduled visits, only VNS parameter settings, concomitant treatment for epilepsy and safety data will be collected

Target follow-up	Baseline	Implant	Follow-up (post implant)					
	−45 to 5 days before implant	0	Titration visit(s)	3 months (±45 days)	6 months (±45 days)	12/24/36 months (±45 days)	Long-term follow-up *Every 12 months until 60 months or study end (±60 days*)*	Unscheduled visits
Informed consent/assent/data privacy	X							
Inclusion/exclusion criteria	X							
Demographics and medical history	X							
VNS Therapy implant/revision/explant		X	*As needed*	*As needed*	*As needed*	*As needed*	*As needed*	*As needed*
VNS Therapy parameter settings		X	X	X	X	X	X	X
Concomitant treatments for epilepsy†	X			X	X	X	X	
Rescue medication use	X			X	X	X	X	
Seizure frequency	X			X	X	X	X	
Maximum seizure-free period	X			X	X	X	X	
Seizure severity/postictal severity	X			X	X	X	X	
Quality of life	X			X	X	X	X	
Quality of sleep (PSQI or CSHQ)‡	X			X	X	X	X	
Healthcare utilisation	X			X	X	X	X	
VNS Therapy feature use (if applicable)			X	X	X	X	X	X
Deaths and AEs related to VNS (if applicable)§		X	X	X	X	X	X	X
Pregnancy reporting form (if applicable)	*As needed*	*As needed*	*As needed*	*As needed*	*As needed*	*As needed*	*As needed*	*As needed*
Device deficiencies (if applicable)		X	X	X	X	X	X	X
Study completion or withdrawal			*At study exit*	*At study exit*	*At study exit*	*At study exit*	*At study exit*	*At study exit*

*During the long-term follow-up phase, subjects will have yearly follow-up visits until 60 months post implant or until study end (whichever comes first).

†Pharmacological and non-pharmacological.

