‡PSQI: Pittsburgh Sleep Quality Index for subjects ≥18 years of age at baseline/CSHQ: Children Sleep Habit Questionnaire for subjects 2–17 years of age at baseline.

§AEs possibly, probably or definitely related to VNS Therapy per investigator assessment (including those with unknown relationship).

AEs, adverse events; CSHQ, Children Sleep Habit Questionnaire; PSQI, Pittsburgh Sleep Quality Index; VNS, vagus nerve stimulation.

Clinical assessments include: average seizure frequency per month for the 3 months prior to each protocol-specified visit and maximum seizure-free period over 90 days prior to each protocol-specified visit. Seizure severity and postictal severity are based on participant-rated categorical outcome (very mild; mild; moderate; severe; and very severe). Quality of life assessment is based on a participant-rated categorical outcome (very good: could hardly be better; pretty good; good and bad parts about equal; pretty bad; or very bad: could hardly be worse). Given the anticipated recruitment and the duration of the study, Likert scales were selected to limit the impact of visit duration on enrolment and participant retention.

On account of previously reported interactions between VNS and sleep apnoea and the limited evidence in this area,^20–22^ quality of sleep assessment was collected through validated scales. Participants who are over 18 years of age at baseline are requested to complete the Pittsburgh Sleep Quality Index (PSQI) at each protocol-specified visit, including baseline.^23^ Participants who are between 2 and 18 years of age at baseline complete the Children’s Sleep Habit Questionnaire.^24–26^ Participants who are less than 2 years of age at baseline are not assessed for sleep quality.

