The design of CORE-VNS allows for a prospective assessment of programmed settings through the titration window. In many people, these settings are collected in electronic records along with other clinical and safety outcomes data. Such records are not collected at titration visits, which do not assess clinical and safety outcomes. To mitigate this, an electronic capture of the programming history from each programming tablet will be used in the registry. These data will be used to develop a clear picture of the titration period from each site and aim to eliminate the risk of missing data fields in titration logs.

Lastly, COVID-19 has impacted this registry both from a recruiting and follow-up perspective. CORE-VNS began in 2018, so until the first quarter of 2020 participants were able to attend follow-up visits in person according to standard programming and titration schedules. During lockdowns imposed during the pandemic, some participants missed titration visits, or these visits were delayed. While participants with newer programming features like scheduled programming may have been less impacted, concern remains regarding the impact of these titration delays on therapeutic efficacy. A subgroup analysis by enrolment year may clarify the extent of this impact.

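### Time-to-response is planned as a Cox analysis, but the visit schedule only brackets response between visits; a discrete-time or interval-censored form would fit the data better

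*Protocol article*

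**What the plan says.** Under Titration guidance and scheduled programming, the protocol article fixes the model and the contrast: "The relationship between time-to-dose and time-to-response will be assessed using a Cox proportional hazard model". The stated aim is to characterise the effect of "rapid titration (titration in <3 months) on clinical outcomes, as opposed to slow titration (>6 months").

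Under Clinical endpoints it sets out when outcome is observed. There is "data collection at baseline as well as 3, 6, 12, 24 and 36 months after implant", with annual visits to 60 months where applicable. Seizure frequency is recorded as "average seizure frequency per month for the 3 months prior to each protocol-specified visit", and the other seizure measure with a look-back is the "maximum seizure-free period over 90 days prior to each protocol-specified visit". Table 2 allows ±45 days at every visit to month 36, for example "12/24/36 months (±45 days").

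Nothing else fills the gaps. The caption of Table 2 limits unscheduled visits to device settings, concomitant epilepsy treatment and safety. Design limitations says that titration visits do not assess clinical outcome. The same section says that COVID-19 affected follow-up and that "During lockdowns imposed during the pandemic, some participants missed titration visits, or these visits were delayed".

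**The concern.** An ordinary Cox model needs one date per event. Here response is a change in a 3-month average read at a visit, so the data hold no response date. They show only the last visit without response and the first visit with it.

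The simplest way to obtain a date is to use the visit date. Calendar differences in attendance would then enter the comparison as differences in speed of response. This does not depend on how the titration groups are formed, and it would remain if they were fixed at baseline.

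The analysis is meant to inform titration guidance. A scheduling artefact could therefore be read as evidence about titration speed.

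**Working it through.** The article gives no event count, power or hazard ratio for this analysis, so there is no figure of its own to reproduce.

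**1. Coverage (from Clinical endpoints and Table 2).** At nominal dates the look-backs span months 0–3, 3–6, 9–12, 21–24 and 33–36.
- Observed: 5 × 3 = 15 of 36 months (42%).
- Not observed: 6–9, 12–21 and 24–33, that is 3 + 9 + 9 = 21 months.
- Moving the 3- and 6-month visits within their windows makes look-backs overlap or reach back before implant. Coverage is then 360 to 450 of 1,095 days (33% to 41%), so 15 months is an upper limit.
- A lasting response that starts in month 13 is first recorded at the 24-month visit.

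**2. Precision of a visit date.** The 3-month visit may fall on day 90 ± 45, that is 45 to 135. The 6-month visit may fall on day 180 ± 45, that is 135 to 225. The same response at the same scheduled visit can thus be dated up to 90 days apart, while the groups are split at 3 and 6 months.

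**3. Mechanism, by hand.** Assume 300 per group, the same 35% response at the first visit in both groups (105 responders each), and all slow titrators seen after all rapid titrators.
- Rapid group's visit date: 105 events, 300 of 600 at risk are rapid. Expected rapid events = 105 × 300/600 = 52.5.
- Slow group's visit date: 105 events, 195 rapid and 300 slow at risk. Expected rapid events = 105 × 195/495 = 41.4.
- Total expected 93.9; observed 105. Rapid titration looks better although response is identical.
- With both groups on one scheduled visit time: expected = 210 × 300/600 = 105, equal to observed.

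This is the extreme case, with no overlap in dates. Individual spread in visit dates weakens it.

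**4. Simulated size.** Cox model (Efron ties) on visit dates, no true difference. Hazard ratio is rapid versus slow.

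| Assumptions | Slow group seen later by | Hazard ratio |
|---|---|---|
| Same response probability per visit, 300 per group, visit SD 12 days | 0 / 10 / 20 / 30 days | 0.99–1.01 / 1.10–1.13 / 1.20–1.21 / 1.28–1.29 (two runs) |
| As above, SD 25 days | 10 / 20 / 30 days | 1.07 / 1.10 / 1.17 |
| As above, SD 25 days, 150 per group | 20 days | 1.07 |
| SD 12 days, 300 per group, only the 3- and 6-month visits late | 20 days | 1.12 |
| SD 12 days, 300 per group, slow group seen earlier | −20 days | 0.83 |
| Exponential response times, 30% or 50% responding by 12 months, 200 per group, visit spread ±15 days | 0 / 7 / 15 / 30 days | 1.00–1.01 / 1.18–1.19 / 1.31–1.36 / 1.40–1.46 |

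Response rates, visit spread, group sizes and shifts are all assumptions; the article gives none of them.

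**5. Alternatives.**
- In the equal-probability setting, a complementary log-log model by visit gave 0.99 to 1.01 for shifts of 0 to 30 days.
- In the exponential setting, a Cox fit on nominal visit time gave 0.95 to 1.01. The drift below 1 arises because the later-seen group has had longer to respond.
- In the exponential setting, an interval-censored exponential fit, which matches how those data were generated, gave 0.99 to 1.01.

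**The case against.** The strongest reply is that the article names a model and not a dating rule. It does not define response for this analysis either. A reader might infer that visit dates will serve as event times, but nothing in the text says so. Such detail usually sits in the statistical analysis plan, which is not shown. The complementary log-log model is itself the grouped-time form of the Cox model, so adopting it carries out the stated intention. All of this stands. It means that the point is a recommendation on the form of the model, not a demonstrated error.

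A reader might also infer that slow titrators had later outcome visits. The article does not show this. The delays it reports concern titration visits, which collect no outcome, and outcome visits are timed from implant. It does say in general terms that COVID-19 affected follow-up, and disruption that slows titration could also delay outcome visits. That makes a difference plausible and no more.

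Nor does the bias necessarily favour rapid titration. It runs against whichever group is seen later, and reverses (0.83) when the slow group is seen 20 days earlier. It would also go too far to say that nothing is known before the 3-month visit, because that visit's look-back nominally covers months 0–3, though only as an average.

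Finally, this is one exploratory analysis in a registry without a power calculation. The article offers a subgroup analysis by enrolment year for the pandemic's effect, but that does not address how response is dated.

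**Conclusion.** The point holds in a conditional form. Response is interval-censored by the visit schedule, and at most 15 of the first 36 months are covered. That follows from the article alone. A spurious hazard ratio would need two further things that the article does not establish: visit dates used as event times in an ordinary Cox fit, and a systematic difference in outcome-visit timing between the titration groups. With equal timing the hazard ratio stays at about 1.

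If both conditions applied, shifts of 10 to 30 days, all within the permitted windows on average, gave hazard ratios mostly between 1.1 and 1.4, with extremes of 1.07 and 1.46. The direction, against the later-seen group, does not depend on the assumptions; the size does. False-positive rates under a later-seen slow group ran from about 6% to 85% depending on visit spread, group size and shift, so none should be quoted as a property of this registry. The sizes of the two titration groups are unknown, since those titrated in 3 to 6 months fall outside the contrast.

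This is a cheap improvement to an exploratory analysis, not a flaw that invalidates the plan.

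**What to change.** In the section on titration guidance and scheduled programming, replace the ordinary Cox analysis of time-to-response with one of the following:

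- a discrete-time proportional hazards model for first observed response by scheduled visit (complementary log-log link, one intercept per visit); or
- an interval-censored proportional hazards model, bounded by the last visit without response and the first visit with it.

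The interval-censored form uses actual dates. It is the safer choice if visit timing proves to differ between the groups, because a by-visit analysis can then drift slightly the other way. Tabulating outcome-visit dates by titration group would show whether this matters.

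Report the result as response by 3, 6, 12, 24 and 36 months, and make no claim about onset between visits.

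The cost is a change of wording and a standard model, with no new data. The downside is a coarser statement on speed of onset.

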### ASMs and VNS Therapy

In accordance with the approved product label, VNS Therapy is prescribed concomitantly with other therapies. Despite this, little guidance has been offered to suggest whether drug–device combination therapies can enhance efficacy or safety outcomes. Polypharmacy contributes to the current lack of evidence, as it creates significant challenges in creating consistent subpopulations for analysis. The size of the CORE-VNS registry may allow insight whether certain drug classes (eg, benzodiazepines; sodium channel blockers) in combination with VNS are associated with more favourable outcomes. The question of whether VNS reduces average drug burden over time will also be explored.

### Concomitant therapies with VNS Therapy

The CORE-VNS inclusion criteria specify that participants must have pharmacoresistant epilepsy. A recent VNS registry has reported a number of people are concomitantly treated with VNS and another non-pharmacological DRE therapy (such as dietary therapy or other neurostimulation therapies) or have previously undergone epilepsy surgery.^29^ Exploring the possible synergistic benefits of VNS with other non-pharmacological therapies is of interest. Given the global scope of the trial and the limited worldwide access to other device-based therapies, it is anticipated that the potential synergistic effect of VNS and ketogenic diet^31^ will be the primary focus in this context. Deep brain stimulation is approved for use in approximately half of the study centres and responsive neurostimulation is approved for use in approximately one-third of the study centres. These devices are not approved for concomitant use with other neurostimulation technologies, so off-label use with VNS is expected to be very infrequent. Pursuant to the statistical analysis plan, interactions between these therapies and VNS will only be assessed if the number of participants within a given subpopulation exceeds 1% of the total study population and will be conducted in accordance with the statistical techniques defined previously. Any participants that receive another device during the follow-up period will be followed normally.

### Healthcare resource utilisation by people receiving VNS

The DRE population uses a disproportionate amount of the healthcare resources accounted for by people with epilepsy, which is characterised in the skewed nature of epilepsy healthcare cost distributions.^32^ Costly ED visits are significant drivers of the healthcare resource utilisation in this population. We will assess, on a regional basis, how VNS impacts ED utilisation and overall healthcare utilisation. We will also assess whether utilisation of scheduled programming can reduce the number of office visits required to titrate patients to dose.

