### Healthcare resource utilisation

The number of seizure-related emergency department (ED) visits and seizure-related hospitalisations, as well as the duration of those stays, that have occurred since the previous visit are collected at each visit. At the baseline visit, these outcomes are collected through the previous 12 months. Clinical visits related to VNS programming are also collected.

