Principal analysis of the full cohort data will occur at 3 years of follow-up and will be summarised using descriptive statistics for the relevant analysis population (mSAF or FAS). Intermediate analysis will also be conducted for the full cohort at each year after implant, and topics of this analysis are further described in the following section. Continuous variables will be summarised using the number of observations, mean, median, SD, minimum and maximum values. Categorical variables will be summarised using the number of observations and percentages. Absolute scores and changes from baseline with 95% CIs will be reported for each clinical endpoint at each follow-up visit. VNS-related adverse events, including serious adverse events and deaths, will be presented by system organ class and preferred term as total counts and percentages. These adverse events will be further described by their relationship to VNS implant and/or stimulation and the current status (eg, ongoing, resolved, death, chronic or unknown).

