### The global safety profile of VNS

VNS has been established as a well-tolerated and safe therapy. This finding has been replicated in multicentre randomised controlled trials, registries, single-centre experiences and case series. Most of the global research experience with VNS, however, has occurred in only a few countries. CORE-VNS presents an opportunity to better understand the safety profile of VNS in multiple regions where it has not been previously studied, especially those regions with more recent access to the therapy. Also, certain device components (such as the newest leads) or features (such as responsive VNS) have not been assessed in a comparative fashion versus previous models of these components in a real-world setting.

Patients involved in the study can elect to undergo a device explantation, for any reason. The rationale for explantation is recorded in the case report form associated with that study event. The explantation surgery case report form includes rationale for the explant, such as: death, adverse event(s), lack of efficacy, VNS Therapy no longer desired, MRI, battery depleted, battery nearing depletion, unknown, other.

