### Design limitations

Although VNS Therapy has been approved for the treatment of DRE for nearly 30 years, systematic evaluation of its use in the real-world setting has been lacking. The clinical benefits of the latest advances in model features have not been well studied. Given the prospective design, international recruitment and scale, CORE-VNS is ideally suited to generate the much needed long-term evidence to inform the optimal use of modern VNS.

Nonetheless, the study has several limitations. The primary limitation in the protocol design is that the registry only explores the effects of VNS in those who receive it. There is no direct comparison with a parallel group who do not receive VNS. Therefore, the incremental benefit of adding the therapy to a treatment paradigm can only be assessed by comparing with the participant’s own baseline.

The registry did not enrol all patients with VNS. While all sequential patients were considered for enrolment, the inclusion criteria for the study required that subjects and caregivers be willing and able to comply with the frequency of study visits, and assent/consent to participate. Because the inclusion criteria were assessed before the creation of any study documentation linked to a potential participant, no study documentation exists to assess the risk of bias from non-included patients, which could potentially impact the generalisability of the results. Finally, this registry is observational and was not specifically designed to address any of the exploratory analyses described here with adequate statistical power. It is expected that the large size of this registry will help to reduce the risk of undersampling.

There are practice-specific differences in implementation of VNS. The manufacturer’s recommendations on titration and programming may not be closely followed at all centres, including some centres and practices included in the CORE-VNS registry. There are many legitimate, person-centred reasons for this interpractice variability (eg, tolerability, lifestyle) and there are also fundamental differences in hospital-led and company-led training between regions (including regions within the same country). These differences in therapy implementation may confound regional assessment of clinical and safety outcomes. In all regional analyses, careful attention will be paid to marked variance in VNS settings (as compared with global averages based on this study and historical VNS registry data).

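### Emergency and hospital use is collected only when seizure-related, so it cannot support a conclusion on overall utilisation; for new implants the before-after change is biased towards VNS

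*Protocol article*

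**What the plan says.** The objective stands in the protocol article, section *Healthcare resource utilisation by people receiving VNS*: "We will assess, on a regional basis, how VNS impacts ED utilisation and overall healthcare utilisation". It carries no restriction by cause.

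What is collected is defined in the methods section *Healthcare resource utilisation*: "The number of seizure-related emergency department (ED) visits and seizure-related hospitalisations, as well as the duration of those stays", recorded at each visit for the time since the previous one. For the reference period, "At the baseline visit, these outcomes are collected through the previous 12 months". One further item is listed: "Clinical visits related to VNS programming are also collected".

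Other device-related information is recorded elsewhere:

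- Table 2 has a row for "VNS Therapy implant/revision/explant", separate from the healthcare utilisation row.
- On explants, *The global safety profile of VNS* says: "The rationale for explantation is recorded in the case report form associated with that study event".
- Under *Statistical analysis*, "VNS-related adverse events, including serious adverse events and deaths, will be presented by system organ class and preferred term as total counts and percentages".

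*Design limitations* states the comparison: "There is no direct comparison with a parallel group who do not receive VNS". Any effect is judged against the participant's own baseline.

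**The concern.** The objective names ED use and overall use, but the ED and hospital data are limited to one cause. That cause is the one the therapy is meant to reduce. An ED visit or admission for a device complication is not seizure-related, so it has no place in the ED and hospital counts. VNS-induced apnoea, which the article itself acknowledges, is one possible example.

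At stake is the wording of a utilisation result. A report that follows the text could present a fall in seizure-related use as a fall in overall use. The opening of *Methods and analysis* says the registry should inform payers and regulators among others, and for them the difference matters.

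**Working it through.** The article gives no utilisation rate, sample size or event count for this objective, so there is no figure to reproduce. The check compares the objective with the collection and then works out the direction of the error.

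**Step 1. Objective against collection**

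| Type of use | Covered by the objective? | Where recorded |
|---|---|---|
| Seizure-related ED visits, admissions, length of stay | Yes | Utilisation item |
| VNS programming visits | Yes | Utilisation item |
| Implant, revision, explant | Yes, as part of overall use | Table 2, separate row |
| ED visits or admissions for device complications | Yes | Not in the utilisation item; the event itself is recorded as a VNS-related adverse event |
| ED visits or admissions for other causes | Yes | No stated source |

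The third and fourth rows show that device-related procedures and events are recorded, but outside the utilisation item. The article does not say that the procedure or adverse event forms hold ED visits, admissions or bed-days. For the last row, Table 2 limits adverse events to those judged related to VNS or of unknown relationship, so unrelated admissions would not appear there either.

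**Step 2. Direction of the error**

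Let S be the seizure-related ED and hospital rate and V the device-caused rate, with 0 for before implant and 1 for after.

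- Change estimated from the planned counts: S1 − S0.
- Change counting both kinds: (S1 − S0) + (V1 − V0).
- Error of the planned counts: −(V1 − V0).

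*New implants.* V0 = 0 and V1 ≥ 0, so the error is −V1. It is never against VNS.

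*Replacement implants.* These participants already carried a device in the baseline year, so V0 may exceed zero. The sign of V1 − V0 is then unknown.

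The baseline covers 12 months and follow-up covers the interval between visits. Rescaling to yearly rates does not help, because V is missing from the count itself.

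**Step 3. Illustration (all rates assumed, none from the documents)**

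New implants, with S0 = 1.00 and S1 = 0.70 per person-year. The planned counts give (0.70 − 1.00)/1.00 = −30%.

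| V1 per person-year | Change counting both |
|---|---|
| 0.05 | (0.75 − 1.00)/1.00 = −25% |
| 0.10 | (0.80 − 1.00)/1.00 = −20% |
| 0.20 | (0.90 − 1.00)/1.00 = −10% |
| 0.30 | (1.00 − 1.00)/1.00 = 0% |

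Replacement implants, same S0 and S1, so the planned change is −0.30 per person-year:

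- V0 = 0.05, V1 = 0.10: −0.30 + 0.05 = −0.25. The planned counts overstate the fall.
- V0 = 0.10, V1 = 0.05: −0.30 − 0.05 = −0.35. The planned counts understate it.

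**The case against.** The strongest reply is that this is a wording mismatch in a condensed article. The analysis is exploratory and outside the principal analysis, and the absence of a control group is already admitted. How the recorded items combine into a utilisation variable may be settled in the full protocol or the SAP, and nothing in the article says the procedure and adverse event forms will be left out.

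Part of this stands. The article is only silent on whether those forms will be used, and that silence is no finding. But the restriction to seizure-related ED visits and admissions is stated explicitly and governs collection. An analysis plan cannot recover visits that were never recorded.

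Three stronger readings are tempting, and the documents do not support them.

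- *All use that VNS causes is left out.* Programming visits are counted as utilisation, and the article plans to examine office visits for titration. Procedures and VNS-related events are recorded elsewhere.
- *The result is fixed in advance in favour of the device.* The estimate can still go either way. It is biased for new implants, by an unknown amount, and replacement implants may differ.
- *The implant alone outweighs any saving.* Suppose admissions fall from 0.5 to 0.35 per year. Over 3 years the saving is 0.15 × 3 = 0.45, against 1.0 procedure per person, a net +0.55. Over 5 years the saving is 0.15 × 5 = 0.75, a net +0.25. Both rest on assumed rates and on treating the implant as an admission. Every enrolled participant is known to have had an implant, so this term is hidden from nobody.

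**Conclusion.** The point holds in a limited form. The counts in the utilisation item describe seizure-related ED visits and hospitalisations and VNS programming visits. They cannot support the stated objective on unqualified ED use and overall utilisation.

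In a before-after comparison without a control group, leaving device-caused ED and hospital use out of the count biases the change towards VNS for newly implanted participants. The bias equals the omitted rate, which the documents do not allow to be computed. The percentages above show direction only. For replacement implants the direction is uncertain.

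This rests on two readings of the text: that the seizure-related qualifier applies to ED visits and to hospitalisations, as written, and that the baseline year uses the same definitions. It does not touch the seizure or safety summaries.

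**What to change.** In *Healthcare resource utilisation by people receiving VNS*, restrict the objective and the conclusion to seizure-related ED visits and hospitalisations, and VNS programming visits. Make no claim about overall use.

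Beside these counts, report separately:

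- the number of implant, revision, explant and replacement procedures;
- the number of VNS-related serious adverse events, with hospital care where the forms record it.

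Split the table by new and replacement implant, because the bias differs between them. Do not add the items into one total. ED visits, admissions, operations and clinic visits have no common unit, and an admission recorded both as seizure-related and as VNS-related would count twice.

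The cost is one changed sentence and one extra table. Enrolment has closed, but the change needs no new data as long as hospital care is shown only where it is already recorded. The price is a narrower, and possibly less favourable, utilisation statement.
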